Health status	HF registry	T0, T1*, T2	SF-36 or SF-12 questionnaire (subset of SF-36)^54^: a validated patient-reported survey of patient health. Both questionnaires consist of eight sections with scores: vitality, physical functioning, bodily pain, general health perceptions, physical role functioning, emotional role functioning, social role functioning and mental health. Each score is transformed into a scale of 0–100 on the assumption that each question carries equal weight. The lower the score, the more disability.
Health-related quality of life	HF registry	T0, T1*, T2	SF-36 or SF-12 questionnaire. QALY will be calculated based on the SF-6D, a model in which a single, preference-based score can be directly calculated for the SF-36 and SF-12.^55^ Scores range from 0.0 (worst health state) to 1.0 (best health state).
Healthcare utilisation	External data source, EHR	T1, T2	Healthcare utilisation based on (1) the number of outpatient visits, plus (2) the number of visits to the general practice related to HF.

*The HF registry collects data standard at baseline (T0), after 6 months (T1) and after 12 months (T2). The RELEASE-HF study conforms to the timeframes of the HF registry. Therefore, data will be collected at 6 months, although the outcome measurements are after 12 months.

†The HF registry defines telemedicine as telemonitoring.

EHR, electronic health record; GP, general practitioner; HF, heart failure; ICD, implantable cardioverter defibrillator; NYHA, New York Heart Association; QALY, quality-adjusted life year; RELEASE-HF, REsponsible roLl-out of E-heAlth through Systematic Evaluation – Heart Failure; SF-12, 12-item short form health survey; SF-36, 36-item short form health survey; SF-6D, six-dimensional health state short form.

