The primary outcome model is a linear mixed model with a random intercept for the participating centre and is specified as follows. The outcome is measured in days, and because the final measurement may be less or more than 365 days after baseline, we rescale the number of days of unplanned hospitalisation to the number of days under follow-up to 365 days. The outcome is computed by subtracting the days of unplanned hospitalisation or death from 365. The earlier described confounding variables are added to the primary outcome model to adjust for confounding. Continuous covariates are modelled using splines. Multicollinearity between confounding variables and the telemedicine status is evaluated. The coefficient for telemedicine in the primary outcome model represents the average treatment effect of offering any telemedicine within 3 months after HF diagnosis compared with not offering telemedicine on days with unplanned HF-related hospitalisation during a year in the population of patients with newly diagnosed HF. Robust SEs are estimated to compute CIs.

For the secondary outcome functional status, a similar approach is taken to estimate the average treatment effect of offering any telemedicine within 3 months after HF diagnosis compared with not offering telemedicine on functional status after 1 year in the population of patients with newly diagnosed HF. For this analysis, the outcome model is a multinomial regression model, and baseline functional status is added as a covariate. The risk difference relative to the reference outcome category is assessed using the predicted outcomes of the primary outcome model offering of telemedicine versus not offering, to obtain the marginal risk difference.^38–40^ Similarly, for the secondary outcomes health status and hrQoL, the outcome model is a probit regression model, with baseline measurements added as a covariate. Healthcare utilisation will be assessed using a Poisson regression model, and all-cause mortality will be assessed using binary logistic regression.

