#### Cost-effectiveness

Costs will be estimated by computing the average costs (using cost guideline provided by the National Health Care Institute) per individual based on the information collected by the NHR and in the interviews with hospitals. Since 2023, Dutch hospitals can claim costs of telemedicine using the National Health Care Institute’s Diagnosis Treatment Combination (DBC). This DBC can be used to estimate the average costs.^37^ A 95% credible interval (CE) will be computed using the percentiles of a Monte Carlo bootstrap analysis with 5000 resamplings. This average cost represents a sum of the costs of telemedicine use, inpatient days, days at intensive care unit, HF-related hospital procedures and outpatient visits. In a secondary analysis, we will re-estimate the average costs and 95% CE using data enriched with VEKTIS data (if linking is available), meaning that the costs of visits to the general practitioner, pharmacy and care at home are also taken into account.

Linkage with CBS may be incomplete for several participants because of missing values or incomplete data sets (eg, twins, different available time windows between registries of collected data). If the number of non-linked participants is below 10%, we will perform multiple imputation; if it is above 10%, we will perform HTA analysis on the complete subset.

Utility values will be estimated using the average hrQoL score collected in the HF registry and, if needed, from the literature. The difference in average QoL score between the group that uses telemedicine versus the group that does not represents the difference in disutility between the groups under the assumption that the collected hrQoL is a good representation of the utility of the particular health state that individuals were in.

Quality-adjusted life years (QALYs) are estimated by multiplying the observed number of follow-up years by the corresponding hrQoL score. Subsequently, the incremental cost-effectiveness ratio (ICER) is computed by taking the ratio between the difference of the costs of the average patient in the telemedicine group and those not in the telemedicine group, and the difference in QALY of both groups, thereby providing the cost per additional QALY gained. The 95% CEs are obtained using the Monte Carlo percentile methods described above. Both deterministic and probabilistic sensitivity analyses will be performed to completely outline uncertainty on individual and combined parameters in the model.

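### QALYs are built on observed follow-up time with no fixed 365-day horizon, so visit timing, and possibly loss to follow-up, can enter the ICER denominator

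*Protocol article*

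**What the plan says.** All references are to the protocol article.

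- **Cost-effectiveness**, on the QALY: "Quality-adjusted life years (QALYs) are estimated by multiplying the observed number of follow-up years by the corresponding hrQoL score".
- **Cost-effectiveness**, on the utility: "Utility values will be estimated using the average hrQoL score collected in the HF registry and, if needed, from the literature".
- **Cost-effectiveness**, on the ICER: the cost difference is divided by "the difference in QALY of both groups, thereby providing the cost per additional QALY gained". Research questions 3 and 4 both use this ratio.
- **Table 1**, health-related quality of life: "QALY will be calculated based on the SF-6D, a model in which a single, preference-based score can be directly calculated" from the SF-36 or SF-12. The readings are collected at T0, T1 and T2, that is at baseline, 6 months and 12 months.
- **Preparation of the statistical model**, primary outcome: the authors recognise that "the final measurement may be less or more than 365 days after baseline" and therefore state that "we rescale the number of days of unplanned hospitalisation to the number of days under follow-up to 365 days".

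The only missing-data rule in the Cost-effectiveness section concerns participants who cannot be linked to Statistics Netherlands (CBS). The Sample size calculation allows for 20% dropout overall.

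**The concern.** A QALY total has a meaning only over a stated period. Here the time factor is whatever follow-up was observed, and the article itself says that this varies around one year. The same problem is corrected for the primary outcome but not for the QALY.

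Two patients with the same health can then receive different QALYs because one was seen later. If observed follow-up stops at the last registry visit, a patient who is alive but no longer registered also loses QALYs. Time lost through death is different: it is a real loss and the formula treats it properly.

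The QALY difference is the denominator of every ICER for research questions 3 and 4, two of the four study objectives. If visit timing or completeness differs between the groups compared, part of the denominator reflects registration practice. Confounder adjustment is not designed to remove this, because the error lies in how the outcome is built. The planned bootstrap and sensitivity analyses are described as expressing uncertainty, not as correcting follow-up time.

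A second, smaller issue is the score that multiplies the time. Three readings are planned, but the text does not settle whether they are averaged into one value or applied interval by interval.

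**Working it through.** **The plan's own figures.** The article gives no QALY, utility or ICER figure to reproduce. I borrow one design figure for scale, the 6.4-day effect (SD 21.1). The sample size built on it reproduces closely. With two-sided 5% (sidedness is not stated) and 80% power, 2 × (1.960 + 0.842)² × 21.1² / 6.4² gives 171 per arm. Dividing by 0.80 gives 214 per arm, 428 in total (430 with the t distribution), against the stated 432. Then 432 × 12 = 5184 and 5184 / 0.80 = 6480, both exact.

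**Assumption.** Utility is taken as constant at 0.70, with 0.60 to 0.80 as the range. These values are mine.

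**1. Visit timing, one survivor.** The stated formula is QALY = (days observed / 365) × utility.

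| Last visit | Utility 0.60 | Utility 0.70 | Utility 0.80 |
|---|---|---|---|
| Day 335 | 0.551 | 0.642 | 0.734 |
| Day 395 | 0.649 | 0.758 | 0.866 |
| Fixed 365 days | 0.600 | 0.700 | 0.800 |

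**2. Visit timing, group difference.** A 7-day difference in mean last-visit date gives 7/365 × 0.70 = 0.013 QALY (0.012 to 0.015). A 14-day difference gives 14/365 × 0.70 = 0.027 (0.023 to 0.031).

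**3. Scale.** The 6.4-day design effect, valued the same way, is 6.4/365 × 0.70 = 0.012 QALY (0.011 to 0.014). This is a rough yardstick: it values each gained day at full utility and each lost day at zero.

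**4. Loss to follow-up, if observed time ends at the last registry visit.** A patient alive all year but last seen at 6 months scores 0.5 × 0.70 = 0.35 instead of 0.70. A difference of 10 percentage points between groups in such losses gives 0.10 × 0.35 = 0.035 QALY (0.030 to 0.040).

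**5. One score or several.** Take assumed readings of 0.60, 0.70 and 0.72 at 0, 6 and 12 months.

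- Area under the curve: 0.5 × (0.60 + 0.70)/2 + 0.5 × (0.70 + 0.72)/2 = 0.325 + 0.355 = 0.680.
- Simple mean of the three: 2.02/3 = 0.673.
- T2 only: 0.720.

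The error in a difference can be larger in relative terms. With 0.60, 0.70, 0.70 against a flat 0.60:

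- The area gives a gain of 0.5 × 0.65 + 0.5 × 0.70 − 0.60 = 0.075.
- The simple mean gives 2.00/3 − 0.60 = 0.067, or 11% less.

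Equal weights over-count T0 and T2, each of which carries a quarter of the area, while T1 carries half.

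**The case against.** The strongest reply is that this is a condensed sentence in an article that frames its outcomes within one year, by authors who plainly know that visits drift around day 365. On that view the missing horizon is an abridgement. I do not think this disposes of the point. The article states a formula and the formula uses observed time, so an analyst following it would not apply the rescaling given for another outcome.

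Other replies do limit what can be claimed.

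- **A reader might infer that the plan fixes a single score per patient.** The text does not go that far. *Corresponding* may mean the score belonging to each interval, and Table 1 provides three readings. This part is an ambiguity. Using T2 alone is nowhere stated; the text speaks of an average.
- **A reader might infer that anyone lost at 6 months is scored as if dead.** That follows only if observed follow-up ends at the last registry visit. Mortality is verified at the Personal Records Database, so follow-up could instead mean time known alive. The article does not say which.
- **A reader might infer that the ICERs will be badly distorted.** The documents show no difference in timing or dropout by telemedicine status, and the 20% dropout is an overall planning allowance. An ICER illustration also depends on what costs do. Assume a true gain of 0.03 QALY and an extra cost of EUR 1000, so 1000/0.03 is about 33,300. Ten extra days add 10/365 × 0.70 = 0.0192 QALY. With cost held fixed the ratio is 1000/0.0492, about 20,300. If costs also accrue, at an assumed EUR 10,000 a year, it is 1274/0.0492, about 25,900.
- **Registry SF-6D data may be sparse.** The plan allows utilities from the literature if needed, so a per-patient area may lean on imputation. This stands as a cost of the fix.

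**Conclusion.** The concern holds in a limited form. The stated QALY formula has no fixed horizon, and the article acknowledges and corrects the same variation for the primary outcome only. Taken literally, a survivor's QALYs move by 30/365 × 0.70 = 0.058 for each 30-day shift of the last visit.

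Bias in the group difference depends mainly on visit timing or dropout differing between groups. That is plausible: registration is voluntary and non-consecutive, telemedicine is not randomised, and for research question 4 the components are assigned by hospital, so local scheduling habits fall directly on the contrast. The documents do not show that it occurs. If it does, a difference of about a week is as large as the design's own 6.4-day effect expressed in QALYs, given the assumed utility. Equal dropout in both groups would not create a difference, but would shrink a real one.

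The choice between one averaged score and interval-specific scores is unclear wording that needs settling. No stated number is wrong. The point should be fixed before the economic analysis. It bears on research questions 3 and 4 and leaves the primary outcome untouched.

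**What to change.** Replace the QALY sentence in the Cost-effectiveness section with a rule of this kind:

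- QALYs are computed per patient over a fixed 365 days from baseline, as the area under the SF-6D readings at T0, T1 and T2 placed at their actual dates (trapezoidal rule).
- A curve that runs past day 365 is interpolated and cut there. For a last reading before day 365, the rule states how the curve is continued to day 365.
- Utility is 0 from the date of death.
- For patients known to be alive with a missing score, the score is multiply imputed and follow-up is not shortened.
- Costs are counted over the same 365 days.

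The cost is one paragraph of text and some extra programming. The three readings and verified mortality are already planned, and the rescaling and the time-until-death summary imply that visit and death dates will be available. The drawback is reliance on imputation where registry SF-6D data are thin. Reporting the number of observed scores per visit and group, and the distribution of last-visit dates by group, would show how much rests on it and whether timing did differ.

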##### Preparation of the statistical model

As a first step, we describe how the overall effect of offering any type of telemedicine versus not offering telemedicine will be estimated. This analysis will subsequently be used for a comparison of telemedicine effects on days alive without unplanned HF-related hospitalisation during 1 year across subgroups.

The cohort is restricted to individuals with newly diagnosed HF, that is, at most 3 months prior to baseline. The exposure contrast is defined as offering any type of telemedicine after first presentation with HF at the hospital outpatient clinic versus patients not offered telemedicine. The telemedicine status for the entire follow-up is defined by 6 months after baseline measurement of telemedicine, used as an observational analogue of an ‘intention to treat’ analysis in which the stopping of telemedicine is disregarded.

Because telemedicine administration is dependent on patient characteristics, confounding by indication will be accounted for. Based on clinical consensus, the following patient-level confounding variables measured at baseline will be adjusted for: age, sex, SES, BMI, NYHA, LVEF, aetiology of HF, systolic blood pressure, diastolic blood pressure, heart rhythm, heart rate, chronic respiratory disorders, OSAS, stroke, extra cardiac arterial vascular pathology, DM, hypertension, anaemia, CKD, malignancy, heart rhythm disorders, depression and thyroid disease (see table 3 and online supplemental material 1).

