##### Research question 3: cost-effectiveness of telemedicine in patient subgroups

For research question 3, costs, utility, QALYs, ICER and willingness-to-pay curves will be computed to estimate the difference in cost-effectiveness between users and non-users of telemedicine in general. Subsequently, the analyses will be repeated to estimate cost-effectiveness in subgroups, similar to the groups defined for research question 2 in the clinical effectiveness analysis.

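### As written, the economic analysis contrasts group averages with no confounder adjustment specified, so objectives 3 and 4 would rest on confounded comparisons

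*Protocol article*

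**What the plan says.** The protocol article's Cost-effectiveness section sets out its estimators one by one.

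- Cost: "Costs will be estimated by computing the average costs (using cost guideline provided by the National Health Care Institute) per individual".
- Utility: "The difference in average QoL score between the group that uses telemedicine versus the group that does not represents the difference in disutility between the" two groups. The one assumption attached is stated as "under the assumption that the collected hrQoL is a good representation of the utility of the particular health state that individuals were in".
- QALY: "Quality-adjusted life years (QALYs) are estimated by multiplying the observed number of follow-up years by the corresponding hrQoL score".
- ICER: "the ratio between the difference of the costs of the average patient in the telemedicine group and those not in the telemedicine group", over the QALY difference between the groups.
- Uncertainty: percentile intervals from 5000 bootstrap resamples, plus deterministic and probabilistic sensitivity analyses on the model parameters.

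Under research question 3 these quantities are computed "to estimate the difference in cost-effectiveness between users and non-users of telemedicine in general", then by subgroup. Under research question 4 they are computed between telemedicine components.

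The clinical part takes a different line. The section on preparing the statistical model says: "Because telemedicine administration is dependent on patient characteristics, confounding by indication will be accounted for". It lists 23 baseline patient variables and enters them in the outcome model. For health status and hrQoL it also adds the baseline measurement. The section on research question 2 adds hospital-level confounders, because the indication for telemedicine is expected to vary between hospitals.

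**The concern.** Telemedicine is not randomised here. Clinicians decide who receives it, and the plan accepts that this choice follows patient characteristics. Characteristics such as age, NYHA class, LVEF and comorbidity can also be expected to drive admissions, procedures and quality of life, and hence both halves of the ICER. A difference in group averages therefore mixes the effect of telemedicine with pre-existing differences between the groups.

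Two of the four study objectives depend on these figures. Effective telemedicine scenarios are to be proposed to hospitals throughout the country, so a confounded cost per QALY could influence practice.

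A related weakness lies in the QALY definition. The primary outcome is rescaled to 365 days because the last measurement may fall earlier or later. The QALY calculation uses observed follow-up time and states no such rescaling.

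**Working it through.** The plan gives no cost, utility or imbalance figure, so it has no number of its own to reproduce on this point. The sample size calculation concerns clinical effectiveness only. The check is a side-by-side reading, followed by an illustration on assumed values.

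**Step 1: where adjustment is stated.**

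| Element | Clinical analysis | Economic analysis |
|---|---|---|
| Estimator | Regression model with random centre intercept (primary outcome) | Averages and differences of averages |
| Patient confounders | 23 listed and entered | None named |
| Baseline hrQoL | Covariate in the hrQoL model | Not mentioned |
| Hospital confounders for components | Listed under research question 2 | None named under research question 4 |
| Unequal observation time | Rescaled to 365 days | Observed years used directly |

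The sections on research questions 3 and 4 borrow only the subgroups and the comparisons from the clinical analysis, not its models or confounders. Their cross-references also look one number off: they cite questions 2 and 3, whereas patient subgroups belong to question 1 and components to question 2.

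**Step 2: what a crude contrast does.** For one severity index with imbalance *d* (users minus non-users, in SD):

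- crude cost difference = true cost difference + *d* × cost slope
- crude QALY difference = true QALY difference + *d* × QALY slope

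Assumed values, none from the documents: true cost difference 500, true QALY difference 0.02 (true ICER 500/0.02 = 25,000), cost slope +1500 per SD, QALY slope −0.05 per SD.

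| *d* | Cost difference | QALY difference | Crude ICER |
|---|---|---|---|
| −0.5 | −250 | 0.045 | negative: telemedicine appears dominant |
| −0.3 | 50 | 0.035 | 1,429 |
| −0.2 | 200 | 0.030 | 6,667 |
| −0.1 | 350 | 0.025 | 14,000 |
| 0 | 500 | 0.020 | 25,000 |
| +0.1 | 650 | 0.015 | 43,333 |
| +0.2 | 800 | 0.010 | 80,000 |
| +0.3 | 950 | 0.005 | 190,000 |

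Adjusting for the index returns 25,000 in every row, by construction. Resampling the crude means centres the interval on the crude value, so 5000 resamples describe sampling error around the wrong quantity. Varying model parameters does not address group comparability either.

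**Step 3: baseline utility.** If users and non-users differ by an assumed 0.02 in SF-6D at baseline and the gap persists, it contributes 0.02 × 1 year = 0.02 QALY, equal to the whole effect assumed in step 2.

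**Step 4: observation time.** Applied literally, "multiplying the observed number of follow-up years by the corresponding hrQoL score" makes QALYs proportional to the time observed. Suppose 5 percentage points more of one group leave observation at mid-year, with an assumed utility of 0.7. The artificial difference is 0.05 × 0.5 × 0.7 = 0.0175 QALY (0.015 at utility 0.6, 0.020 at 0.8).

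**The case against.** The strongest reply is that the article never describes the economic contrasts as unadjusted. The section is a summary, and it mentions a model that it does not describe. Table 1 derives costs from characteristics of the patient, the disease and the treatment, and the Discussion claims extensive confounding correction for the study. A fuller plan might contain the adjustment.

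Part of this stands. A reader might infer that the investigators have decided against adjustment, but the text supports only that none is specified. The rest does not answer the point. The Table 1 entry goes on to list mainly resource-use items to be costed. The Discussion remark is not tied to the economic estimators. The adjusted hrQoL models do not help, because the ICER is fed by average scores rather than by model output. The economic section also goes beyond silence: it names its estimators, and those estimators are crude contrasts.

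Several stronger readings are tempting but unsupported:

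- *The ICER would change sign.* This needs a bias of known size and direction, and the documents give neither. Converting the planned 6.4-day gain into about 0.012 QALY (6.4/365 × 0.7) is no sound benchmark, since it gives hospital days zero utility and leaves out any quality-of-life gain.
- *Loss to follow-up is scored as death.* That is one literal reading. Deaths are verified separately, and the handling of incomplete follow-up is not stated.
- *The bootstrap ignores hospitals.* The article is silent on this, and such detail can be left to the analysis plan.
- *Research question 4 suffers from confounding by indication for telemedicine versus none.* Component contrasts are made among telemedicine recipients and set at hospital level, so the risk there is patient- and hospital-level confounding.
- *The plan promises to remove confounding.* It says that confounding will be accounted for, and the Discussion concedes that it cannot be fully avoided.

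Costs are a secondary outcome and clinical effectiveness is the primary focus. Cost-effectiveness nevertheless makes up two of the four stated objectives.

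**Conclusion.** The point holds as an internal inconsistency. The article treats crude comparisons as confounded in its clinical analysis, then defines incremental cost, utility, QALY and ICER as differences in group averages, with no adjustment specified for research question 3 or 4. Carried out as written, objectives 3 and 4 would rest on confounded contrasts that the planned intervals and sensitivity analyses do not repair. The use of observed follow-up years is a second, smaller problem, and arises if the definition is applied literally.

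The size and direction of the bias cannot be determined from the documents. The figures above rest on assumed effects, slopes, utilities and imbalances. They show only that modest imbalances can matter when the QALY difference is small. The wording should be corrected before the economic analysis is run.

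**What to change.** Amend the Cost-effectiveness section and the sections on research questions 3 and 4 as follows.

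1. Estimate incremental cost and incremental QALY by regression standardisation or inverse-probability weighting, using the confounder set of the clinical model plus baseline SF-6D.
2. For research question 4, add the hospital-level confounders listed under research question 2.
3. Repeat the adjustment within each of the 5000 bootstrap resamples.
4. Compute QALYs over a fixed 1-year horizon from the T0, T1 and T2 scores, with zero after death and incomplete follow-up treated as missing.
5. Base ICERs and willingness-to-pay curves on the adjusted differences, overall, by subgroup and by component.
6. Correct the cross-references to the clinical research questions.

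The cost is mainly wording and analysis code, because the confounders and the SF-36 or SF-12 at T0 are already planned data. Completeness is not assured: the plan foresees taking utilities from the literature if needed and admits that relevant variables may be missing. Intervals will be somewhat wider, more so for research question 4, where components vary only between hospitals and at least 29 hospitals have committed. Adjustment also leaves any unmeasured confounding in place.

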In addition, willingness-to-pay curves will be drawn to highlight the impact of different thresholds on cost-effectiveness outcomes.

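### The bootstrap percentile interval for the ICER cannot be interpreted where the QALY difference may be near or below zero, as is plausible in the subgroup and component analyses

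*Protocol article*

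**What the plan says.** All the relevant text is in the protocol article, under Cost-effectiveness and the two research questions that follow it.

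- **Interval method**, introduced for average costs: "A 95% credible interval (CE) will be computed using the percentiles of a Monte Carlo bootstrap analysis with 5000 resamplings".
- **QALYs:** "Quality-adjusted life years (QALYs) are estimated by multiplying the observed number of follow-up years by the corresponding hrQoL score".
- **ICER:** "the incremental cost-effectiveness ratio (ICER) is computed by taking the ratio between the difference of the costs of the average patient" in the telemedicine and non-telemedicine groups, and the corresponding difference in QALYs, "thereby providing the cost per additional QALY gained".
- **Interval after the ICER definition:** "The 95% CEs are obtained using the Monte Carlo percentile methods described above". Nothing exempts the ICER, and no rule covers resamples with a zero or negative QALY difference.
- **Other uncertainty outputs:** "Both deterministic and probabilistic sensitivity analyses will be performed to completely outline uncertainty on individual and combined parameters in the model", and "willingness-to-pay curves will be drawn to highlight the impact of different thresholds on cost-effectiveness outcomes".
- **Where it is applied:** under research question 3, "the analyses will be repeated to estimate cost-effectiveness in subgroups". Research question 4 does the same for telemedicine components. Both sections list costs, utility, QALYs, the ICER and the curves side by side.

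**The concern.** A percentile interval needs values that can be ranked from favourable to unfavourable. A ratio whose denominator can change sign has no such ranking. More QALYs at lower cost gives a negative ratio, and so do fewer QALYs at higher cost. A positive ratio can be a cost per QALY gained or a saving per QALY lost. The article's gloss of the ICER as a cost per QALY gained holds only while the QALY difference is positive.

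Objectives 3 and 4 ask in whom, and with which components, telemedicine is cost-effective. Those analyses use smaller groups than the overall comparison, so the QALY difference is less certain and its sign more often in doubt. A reader given a subgroup ICER with 95% limits would naturally read the lower limit as the good end and the upper limit as the bad end. In these conditions neither limit has that meaning.

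**Working it through.** **1. The plan's own figures, used only for group sizes.** Effect 6.4 days, SD 21.1, alpha 5% (taken as two-sided), power 80%:

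n per arm = 2 × (1.960 + 0.842)² × (21.1/6.4)² = 170.6, so 171. Allowing for 20% dropout, 171/0.8 = 213.75, so 214 per arm and 428 in total, against 432 stated (agreement within rounding). Then 432 × 12 = 5184 and 5184/0.8 = 6480, both as stated. After 20% dropout, 5184 × 0.8 = 4147 are analysed. A quarter of that, taken as an illustrative subgroup, is 1037.

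**2. Likely size of the denominator.** If QALYs move only through the 6.4 days, the gain is at most 6.4/365 = 0.0175 QALY. At an assumed utility of 0.7 it is 0.7 × 0.0175 = 0.0123. The article gives no QALY or cost difference and no SD for either.

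**3. How often the sign is in doubt.** With two equal groups, SE = SD × √(4/n). The share of resamples with a QALY loss is about Φ(−difference/SE). Above 2.5%, the 95% interval for the QALY difference includes zero.

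| Estimated QALY difference | Assumed QALY SD | n = 4147 | n = 1037 |
|---|---|---|---|
| 0.0123 | 0.10 | <0.1% | 2.4% |
| 0.0123 | 0.20 | 2.4% | 16% |
| 0.0123 | 0.30 | 9% | 26% |
| 0.0175 | 0.10 | <0.1% | 0.2% |
| 0.0175 | 0.20 | 0.2% | 8% |
| 0.0175 | 0.30 | 3% | 17% |

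Example: SE = 0.20 × √(4/1037) = 0.0124; 0.0123/0.0124 = 0.99; Φ(−0.99) = 16%.

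Across repeated studies at SD 0.20, the QALY interval would include zero with probability about Φ(1.96 − true gain/SE). For n = 1037 this is 83% (gain 0.0123) or 71% (0.0175). For n = 4147, where SE = 0.0062, it is 49% or 20%.

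**4. The ratio cannot tell opposite results apart.** Reversing the sign of both differences leaves the ratio unchanged, so the two mirror-image results below have the same ratio distribution under the normal approximation. Assumptions: QALY SD 0.20, cost SD €10,000, correlation −0.2, n = 1037, illustrative threshold €50,000 per QALY.

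| | +0.01 QALY, −€500 | −0.01 QALY, +€500 |
|---|---|---|
| Point ICER | −50,000 | −50,000 |
| Simulated 95% percentile interval | −584,000 to 510,000 | −572,000 to 496,000 |
| Net benefit = 50,000 × QALY difference − cost difference | +1000 | −1000 |
| Probability net benefit > 0 | 85% | 15% |

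The small gap between the two ICER intervals is simulation noise. For net benefit, the SE of 50,000 × QALY difference is 50,000 × 0.01242 = 621, and the SE of cost is 10,000 × √(4/1037) = 621. The combined SE is √(621² + 621² + 2 × 0.2 × 621 × 621) = 962, and Φ(1000/962) = 85%.

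**5. Mixing within one interval.** With +0.01 QALY and +€500, 432 per group and cost SD €12,000, the simulated ICER interval is about −717,000 to 801,000. Of the negative ratios, 43% are worse-and-dearer draws and the rest better-and-cheaper.

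**6. Where the problem disappears.** With +0.05 QALY and +€500, 2592 per group and the same SDs as in step 5, no draw has a QALY loss. The interval is about −3,100 to 25,500, and it ranks properly.

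**The case against.** The strongest reply is that the ICER interval is one output among several. Willingness-to-pay curves are planned overall and named again for research questions 3 and 4, next to costs and QALYs. If they are acceptability curves from the same resamples, they give the probability of positive net benefit at each threshold, which is what separates the mirror cases. This stands, and it confines the defect to the ICER interval. It does not withdraw that interval, because the curves are added to it. The sensitivity analyses do not change how the ratio is summarised either.

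Three stronger readings are tempting, and the document or the figures do not support them.

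- **That research question 3 rests on comparing subgroup ICERs or their intervals.** No section says so; the outputs are listed together.
- **That the interval would pass off a harmful result as cost-effective.** With a true −0.02 QALY and +€500 at n = 4147, the ICER interval lies wholly below €50,000 in about 83% of simulated studies. In every one of those the QALY interval is wholly below zero, so a reader who also has the QALY result would see it.
- **That the interval generally under-covers.** Coverage is about 98% at a gain of 0.01 QALY. It falls to roughly 87% to 91% only near zero (0.002 QALY, n = 1037). The failure is mainly of meaning.

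It is also fair that the sentence on 95% CEs covers more than the ICER, that percentile intervals are sound for costs and QALYs, and that the article puts its primary focus on clinical effectiveness. Bootstrap plots and similar reporting detail can properly sit in an analysis plan that is not shown. The unrestricted percentile interval, however, is stated here.

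**Conclusion.** The point holds for the ICER interval only. As written, the plan applies percentiles to a ratio without restriction. Where the QALY difference may be near or below zero, the resulting 95% limits do not run from favourable to unfavourable. That follows from the form of the ratio and needs no assumed figure.

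How often it would matter does depend on assumptions: QALY SD 0.10 to 0.30, equal groups, a quarter-sized subgroup, and QALYs moving only through the 6.4 days. On these, between 0.2% and 26% of subgroup resamples show a QALY loss (8% to 16% at SD 0.20). The condition is therefore plausible for the research question 3 subgroups. It is also plausible for the research question 4 contrasts, which use telemedicine recipients only and whose size the article does not give. The overall comparison is less exposed, and a clearly positive QALY difference removes the problem. The cost-effectiveness analysis as a whole is not invalidated. This is a worthwhile correction to one reported quantity.

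**What to change.** In the Cost-effectiveness section, replace the sentence on 95% CEs that follows the ICER definition with a rule to this effect:

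- Limit percentile intervals to incremental costs and incremental QALYs.
- For each comparison, subgroup and component, report incremental net monetary benefit (threshold × QALY difference − cost difference) with its bootstrap 95% interval, at the thresholds used for the willingness-to-pay curves.
- Give the ICER as a point value with its quadrant of the cost-effectiveness plane named. Add an interval only when the QALY-difference interval excludes zero. Naming the quadrant is still needed then, because that interval may lie wholly below zero.
- Make any comparison between subgroups on net monetary benefit.

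It would also help to state that the willingness-to-pay curves are acceptability curves from the same resamples, if that is the intention.

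The same 5000 resamples serve, so the cost is a few sentences of text and no new data. The one small drawback is that thresholds must be named; the planned curves already range over thresholds.
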